## Abstract

**Background:**

Spondylolisthesis is the major cause of refractory low back pain. There are many studies of the surgical treatment of spondylolisthesis, but few of conservative treatments. There is also no optimal conservative treatment protocol, however, low back pain caused by low-grade spondylolisthesis is controlled with non-surgical pain management. Acupuncture has become a useful method for treating low back pain, but there has not been any study of its efficacy in relation to spondylolisthesis. This study was designed to establish the feasibility of a randomized controlled trial and the safety of acupuncture for low back pain due to low-grade spondylolisthesis.

**Methods/Design:**

The study is a randomized controlled pilot clinical trial of five weeks duration. Fourteen patients will be recruited and randomly allocated to two groups: an acupuncture plus interlaminar epidural steroid injection group (experimental group), and an interlaminar epidural steroid injection group (control group). All patients will be administered an interlaminar epidural steroid injection once a week for three weeks (three injections in total), but only the experimental group will receive additional treatment with three acupuncture sessions a week for three weeks (nine acupuncture sessions in total). The primary outcome will be measured by the visual analogue scale (VAS). Our primary end point is three-week VAS. The secondary outcome will be measured using the PainVision system, the short-form McGill Pain Questionnaire, and the Oswestry Disability Index. Assessments will be made at baseline and at one, three and five weeks thereafter (that is, the five-week assessment will be made two weeks after treatment cessation).

**Discussion:**

This randomized controlled pilot trial will inform the design of a further full-scale trial. The outcomes will provide some resources for incorporating acupuncture into existing pain management methods such as interlaminar epidural steroid injection in low-grade spondylolisthesis.

**Trial registration:**

This trial is registered with the US National Institutes of Health Clinical Trials registry:
NCT01909284.

## Background

Spondylolisthesis is defined as anterior migration, or slippage, of a vertebral body relative to the next caudad vertebral segment
[1]. Spondylosis and spondylolisthesis occur most commonly in the fifth lumbar vertebral body, but may occur at more cephalad lumbar levels. Patients with L4 spondylosis and spondylolisthesis are more frequently symptomatic
[2,3]. The symptoms clinically associated with spondylolisthesis are low back pain and pain, numbness, or weakness in the legs or lower extremities
[4]. The classification systems of Wiltse-Newman
[1] and Marchetti and Bartolozzi
[5] are the most widely used. In terms of describing the actual severity of spondylolisthesis, the Meyerding scale is the most widely recognized method. The magnitude of spondylolisthesis is measured by dividing the slip distance by the caudad body width and expressed as a percentage. The slip percentage is then categorized according to the Meyerding scale as follows: Grade 0, no slip; Grade I, 1 to 25%; Grade II, 26 to 50%; Grade III, 51 to 75%; Grade IV, 76 to 100%; Grade V: complete slippage. Both the slip percentage and Meyerding grade are reliable measures of severity
[6,7].

Many patients with low-grade spondylolisthesis (Meyerding grade 0, I, II) can be treated conservatively
[8]. Most patients with spondylolisthesis do not worsen with time and rapid deterioration is very rare
[9]. Physical therapy and pain management are the mainstays of conservative treatment, and should be the initial course of action in most cases of spondylolisthesis, with or without neurological symptoms
[8]. Most physicians begin with antiinflammatory medications and physical therapy, including aerobic conditioning, provided there are no gastrointestinal contraindications. If symptoms persist beyond four to six weeks, patients may benefit in the short term from a course of epidural steroid injections. Benefits may include reduced lower back and radiculopathy-associated pain
[4,10].

Acupuncture has become a popular alternative treatment modality for patients with low back pain, which is the major symptom of spondylolisthesis. Indeed, acupuncture has been shown to be effective in relieving low back pain
[11,12]. Leibing *et al.*[13], Haake *et al.*[14], and Brinkhaus *et al.*[15] all reported a significant difference in their primary outcome measures–Visual Analog scale (VAS), Roland Morris Disability Questionnaire, and McGill Pain Index. Witt *et al.*[16] also reported a significant improvement in pain, function, and quality of life after acupuncture treatment when compared to routine care, at three months. However, no published trials have evaluated the efficacy and safety of acupuncture in patients with low back pain due to spondylolisthesis.

In the evaluation of the clinical and radiographic result of the transforaminal lumbar interbody fusion in degenerative and isthmic lower-grade spondylolisthesis, there were 7.6% serious postoperative complications observed, which required operative revision
[17]. Acupuncture would be helpful in patients with spondylolisthesis as a safe conservative treatment without severe adverse events as can happen in some surgical procedures, such as transforaminal lumbar interbody fusion. The primary aim of this trial is to establish the feasibility of a randomized controlled trial and the safety of acupuncture for reducing low back pain due to low-grade spondylolisthesis and improving function compared with usual interlaminar epidural steroid injection.

### Hypotheses

In this randomized controlled two-arm clinical trial, we will evaluate the effect of acupuncture as an adjunct therapy to spondylolisthesis. The primary hypothesis is that acupuncture treatment in addition to interlaminar epidural steroid injection reduces pain (as measured by VAS) significantly more than interlaminar epidural steroid injection only. The secondary hypotheses are that: the score of the PainVision system (PS-2100, Nipro Corporation, Osaka, Japan), is significantly lower in the experimental group than that in the control group; additional acupuncture treatment reduces the score on the short-form McGill Pain Questionnaire (SF-MPQ) significantly more than interlaminar epidural steroid injection alone; interlaminar epidural steroid injection combined with acupuncture is significantly better than interlaminar epidural steroid injection alone in reducing the score on the Oswestry Disability Index (ODI).

## Methods/Design

### Design

The study is a randomized controlled pilot clinical trial. It is designed to assess the efficacy and safety of acupuncture treatment in patients with low back pain due to low-grade spondylolisthesis. The protocols used adhere to the principles of the Declaration of Helsinki and have been approved by the institutional review board of Daegu Catholic University Hospital (IORG0004453), where the study will take place. The trial is registered with the US National Institutes of Health Clinical Trials registry. Written consent will be obtained from each participant before any treatment is given.

The outcome assessment and statistical analyses will be performed by professionals blinded to the assignment of patients. The trial process is presented in Figure 
1. The trial will run for five weeks. Patients will be allocated to two groups; the control group will only receive three interlaminar epidural steroid injections and the experimental group will receive all three steroid injections as well as nine acupuncture sessions (three sessions a week forthree weeks). Assessments will be made at baseline, and again at one, three and five weeks thereafter. The week five assessment will be performed two weeks after treatment cessation.

**Figure 1 F1:**
[figure not shown]
A flow chart of the trial process.

### Recruitment

Participants will be recruited through advertisements on hospital websites and bulletin boards. If patients are interested in participation, they will be invited to visit the hospital for a screening meeting. Their eligibility will be determined by an anesthesiologist through physical and radiological examinations. If eligible, they will be guided through the informed consent process. After written consent is obtained, a study researcher will randomly allocate the participants to one of the two groups. Treatments will be scheduled after randomization.

### Participants

One of the main objectives of this study is to provide an estimate of the sample size required for the full-scale randomized controlled clinical trial. We plan to recruit 14 patients into this pilot study. A target of 14 patients with spondylolisthesis has been set.

The inclusion criteria are that participants must: be aged 18 to 65 years, have Meyerding Grade I to II spondylolisthesis, have low back pain of at least one-year duration, be available for possible follow-up during the clinical trial, and provide written informed consent voluntarily.

The exclusion criteria are: cauda equina syndrome, persistently exacerbated symptoms, progressive neurologic signs (sensory or motor changes); previous spine surgery; senile dementia, impaired cognitive function or other cerebral disease, severe psychiatric or psychological disorders; severe, concomitant disease (neuromuscular scoliosis, neurodegenerative disease); all contraindications to corticosteroid injection (e.g., insulin-dependent diabetes); alcohol/drug abuse; significant renal or hepatic disease; pregnant, lactating or planning a pregnancy; hypersensitive reaction to acupuncture treatment; inability to comprehend or express oneself in the Korean language; an individual deemed to be ineligible by a physician; or refusal to participate in the trial or to provide informed consent.

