### Randomization

Patients will be randomized using a computerized random number generator by an independent statistician blinded to patient assignment. Block randomization will be performed once a participant is confirmed to be eligible and their written informed consent has been obtained.

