### Statistical analysis

The statistical significance level will be set at 5%, and the data will be analyzed using intention-to-treat and per protocol approaches. Data will be processed with the last observation carried forward method for the intention-to-treat analysis, and will be performed using IBM SPSS Win ver. 19.0 statistical software (IBM Co., Armonk, NY, USA).

All demographic and clinical characteristics of the subjects (such as sex, age, and weight) will be processed based on descriptive analyses. Quantitative data will be presented as average, standard deviation, median value, and range. Qualitative data will be presented as the frequency and percentage. The study will identify the comparative equivalence of demographic variables and clinical characteristics between the experimental and control groups.

In order to identify differences in VAS, PainVision scores, SF-MPQ and ODI scores between the experimental and control group based on time (baseline, weeks one, three and five), a repeated-measure twofactor analysis will be performed to identify differences between groups, differences within each group based on time, and the effects of the interaction of the variables based on group. If the interaction between group and time is statistically significant, the point at which the pattern of results between the two groups changes will be checked.

The Chi-square test will be used to compare groups and the incidence frequency of adverse events related to acupuncture and interlaminar epidural steroid injection.

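### The pilot aims at feasibility, safety and a full-scale sample size, but its VAS analysis is a 5% superiority test in 14 patients that does not directly estimate the week-3 difference

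*Protocol article*

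**What the plan says.** **Aims.** The Background section states: "The primary aim of this trial is to establish the feasibility of a randomized controlled trial and the safety of acupuncture". The Participants section adds that a main objective is to "provide an estimate of the sample size required for the full-scale randomized controlled clinical trial". The abstract and the Discussion say that the pilot will inform a full-scale trial.

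**Hypotheses.** The primary hypothesis is that acupuncture added to the injection "reduces pain (as measured by VAS) significantly more than interlaminar epidural steroid injection only". Three secondary superiority hypotheses follow, for PainVision, SF-MPQ and ODI. The Design section also describes the study as assessing efficacy.

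**End point.** The Primary outcome measurement section makes VAS at week 3 the primary end point.

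**Analysis.** The Statistical analysis section states: "The statistical significance level will be set at 5" (per cent). All four outcomes get a two-factor repeated-measures analysis over baseline and weeks 1, 3 and 5. It tests group, time and their interaction, and individual time points are examined if the interaction is significant. The section also plans mean, SD, median and range for quantitative data, within its paragraph on patient characteristics.

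**Size.** "We plan to recruit 14 patients into this pilot study". The abstract says: "Fourteen patients will be recruited and randomly allocated to two groups". Randomization is in blocks, with no allocation ratio stated.

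**The concern.** The aims call for estimation: how large and how variable the week-3 VAS difference is, and how well the trial runs. The hypotheses and the planned analysis call for a verdict on superiority instead. The two do not fit, for two reasons.

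First, with 14 patients a 5% test cannot separate a worthwhile effect from none unless the effect is very large. A non-significant result could then be taken as evidence against acupuncture. A significant one would tend to carry an exaggerated difference into the planning of the next trial.

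Second, the analysis does not target the primary end point. The group effect averages over all four time levels, including baseline, where randomization makes the expected difference zero. The interaction is a joint test over all time points. Neither gives the week-3 difference. That time point is examined separately only if the interaction is significant, which is unlikely at this size unless the effect is large.

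**Working it through.** **Inputs from the protocol.** Total 14, two groups, 5% level, VAS on a 10 cm scale, end point at week 3.

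**Assumptions.** Equal split (7 per arm), two-sided test, and VAS SD between 1.5 and 3 cm. The protocol gives no power, target difference, SD or dropout rate, so the figure of 14 cannot be reproduced.

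**1. Power of a simple week-3 comparison.** The standard error of the standardised difference is √(2/7) = 0.535. The t critical value on 12 df is 2.179. Power comes from the noncentral t distribution with noncentrality d/0.535.

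| True standardised difference d | Power, 7 per arm | Power, 6 per arm |
|---|---|---|
| 0.5 | 14% | 12% |
| 0.8 | 28% | 24% |
| 1.0 | 41% | 35% |
| 1.5 | 73% | 65% |
| 2.0 | 93% | 88% |

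Power of 80% at 7 per arm needs d = 1.63. For SDs of 1.5, 2, 2.5 and 3 cm this is 2.4, 3.3, 4.1 and 4.9 cm on the 10 cm scale.

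**2. Allowance for baseline.** With a baseline to week-3 correlation of 0.5 (assumed), adjustment multiplies the SD by √(1 − 0.5²) = 0.866. The detectable d becomes 1.63 × 0.866 = 1.41, about 1.4.

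**3. Overstatement given significance.** Significance requires an observed standardised difference above 2.179 × 0.535 = 1.16. If the true d is 0.5, simulation shows that the significant results average a difference of about 1.25 true SDs. That is 1.25/0.5 = 2.5 times the truth.

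**4. Dilution by the baseline level.** If the true difference is zero at baseline and δ at weeks 1, 3 and 5, the group effect in the repeated-measures analysis targets (0 + δ + δ + δ)/4 = 0.75δ, not δ.

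**5. Precision of the difference.** The 95% half-width is 2.179 × 0.535 × SD = 1.16 × SD. For SDs of 1.5, 2, 2.5 and 3 cm this is 1.7, 2.3, 2.9 and 3.5 cm.

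**6. Precision of the SD.** On 12 df the 95% limits are s × √(12/χ²), with χ² quantiles 23.34 and 4.40, giving 0.72s to 1.65s. Required n is proportional to the variance, so it runs from 12/23.34 = 0.51 to 12/4.40 = 2.72 times the calculated n, about a 5.3-fold range. For illustration, a target difference of 1.5 cm and an SD of 2.5 cm (both assumed) give 44 per arm at 80% power. The limits move this to about 23 to 120 per arm.

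**The case against.** The strongest reply is that this is a condensed article about a study repeatedly called a pilot, and that the derivation of the full-scale sample size may be left to the full protocol or analysis plan. That stands: the missing derivation is not an error here. Four stronger readings are tempting and should be set aside.

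- **That only significance tests will come out, with no variance estimate.** The Statistical analysis section plans means and SDs. The sentence sits in the paragraph on patient characteristics but is worded for quantitative data generally, so an SD for week-3 VAS will probably be available.
- **That the full-scale trial will be sized on the pilot's SD and difference at face value.** Nothing says so; the document is silent on how they will be used. The range in step 6 describes the SD's uncertainty. It does not show a planning error.
- **That a non-significant result would cancel the full-scale trial.** No go/no-go rule tied to p < 0.05 is stated.
- **That the pilot can decide nothing.** This is a matter of degree: an effect of about 1.6 SD or more would be detected with about 80% power or better.

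It is also fair that 7 per arm is inferred and that the power figures are for an unadjusted test. Step 2 shows that adjustment helps but still leaves a very large detectable effect.

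What the reply does not remove is the contradiction in the stated text: estimation aims on one side, and on the other superiority hypotheses and a 5% analysis that does not isolate the declared end point.

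**Conclusion.** The point holds as a mismatch between the stated aims and the stated hypotheses and analysis. The repeated-measures test neither directly estimates the week-3 VAS difference nor has useful power for the superiority hypothesis: 14% at d = 0.5, 28% at d = 0.8, and 80% only at about d = 1.6 (about 1.4 with baseline adjustment). Non-significance would be uninformative, and significance under a moderate true effect would overstate it. These figures rest on an equal split, a two-sided test and, for the adjusted figure, an assumed correlation of 0.5. The SD will be imprecise (0.72 to 1.65 times the estimate) but can be used if its uncertainty is shown. This should be corrected before the data are read; it does not prevent the pilot from running.

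**What to change.** 1. Make the main VAS analysis the week-3 difference between groups adjusted for baseline VAS (ANCOVA), with a 95% confidence interval. The repeated-measures analysis can stay as a supporting description.
2. Report the adjusted week-3 SD with its confidence interval.
3. Label all p-values exploratory, and reword the Hypotheses section so that no efficacy conclusion rests on p < 0.05.
4. State that the pilot's observed difference will not be the target difference for the full-scale trial.

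Sizing the full-scale trial on an upper confidence limit of the SD is an optional convention, not a required correction. The one-sided 80% limit, for example, gives SD × 1.24 and so n × 1.54.

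**Cost.** Items 1 to 4 need wording and one analysis of data already being collected, with no extra patients. The pilot gives up a confirmatory efficacy claim, which 14 patients could support only for a very large effect.

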### Randomization

Patients will be randomized using a computerized random number generator by an independent statistician blinded to patient assignment. Block randomization will be performed once a participant is confirmed to be eligible and their written informed consent has been obtained.

### Interventions

Patients will be randomly divided into two treatment groups: an experimental group (acupuncture plus interlaminar epidural steroid injection group) and a control group (interlaminar epidural steroid injection group). The interlaminar epidural steroid injections will be administered once per week for three weeks (three times in total) and the acupuncture sessions performed three times per week for three weeks (nine times in total).

### Interlaminar epidural steroid injection

The lumbar interlaminar epidural injections will be administered by an anesthesiologist under fluoroscopy in a sterile procedure room in an outpatient pain management department. The lumbar interlaminar epidural space will be identified by the loss of resistance technique and by fluoroscopic visualization with confirmation with a non-ionic contrast medium. The epidural space will be entered at the level of spondylolisthesis or one space above/below the level of spondylolisthesis. After confirmation of needle placement, 10 mL mepivacaine hydrochloride 0.1% (preservative free) and 5 mg non-particulate dexamethasone will be administered by injection.

### Acupuncture treatment

The following acupoints will be used: GV3 (unilateral), BL23, BL24, BL25, GB30, GB31, BL40, and BL60 (bilateral). In total, 15 acupoints will be used. Sterilized disposable acupuncture needles (DongBang Acupuncture Inc., Sungnam, Korea) 0.25 mm × 40 mm in size will be manually inserted into each of the 15 acupoints. After needle insertion, the Deqi sensation will be induced by manual stimulation, and four acupoints (bilateral BL23, BL25) will be stimulated by an electro-acupuncture device (ES-160, Ito Co. Ltd., Tokyo, Japan). The needles will be inserted for 20 ± 5 minutes and then removed.

### Data collection

In this study, the primary outcome will be measured by VAS. The secondary outcome will be measured by the PainVision system, the SF-MPQ and ODI. Both the primary and secondary outcomes will be measured at baseline, and at one, three and five weeks thereafter. The schedule of treatment and outcome assessments is presented in Table 
1.

**Table 1 T1:** Schedule of treatments and outcome measures throughout the trial

		**Baseline**	**Treatment period**									**Follow-up period**	
		**0 week**	**1 week**			**2 week**			**3 week**			**4 week**	**5 week**
Measures	VAS	√	√						√				√
	Pain Vision	√	√						√				√
	SF-MPQ	√	√						√				√
	ODI	√	√						√				√
	Safety	√							√				
**Treatments**	Interlaminar epidural steroid injection		√			√			√				
	acupuncture		√	√	√	√	√	√	√	√	√		

*ODI*, Oswestry Disability Index; *SF-MPQ*, short-form McGill Pain Questionnaire; *VAS*, visual analogue scale.

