### Primary outcome measurement

#### VAS

Pain intensity will be assessed using a10 cm VAS of subjective pain assessment. Each patient will rate their pain on a scale of 0 to 10 (0 being an absence of pain and 10 being the worst pain imaginable)
[18,19]. VAS measurements will be made at baseline, and at one, three and five weeks. Our primary end point is three-week VAS.

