### Safety

We will confirm the safety of acupuncture by determining the red blood cell (RBC) count, hemoglobin level, platelet count, mean corpuscular volume (MCV), mean corpuscular hemoglobin (MCH), mean corpuscular hemoglobin concentration (MCHC), hematocrit (Hct), total white blood cell (WBC) count, erythrocyte sedimentation rate (ESR), aspartate aminotransferase (AST), alanine aminotransferase (ALT), serum urea nitrogen (BUN), creatinine level, serum sodium level, serum potassium level, and serum chloride level. All patients were evaluated two times, including the screening visit and after the termination of acupuncture.

Any reported adverse events will be recorded throughout the study and vital signs will be monitored at each visit. The patients will be requested to voluntarily report information about adverse events, and the researcher will confirm the occurrence of adverse events through methods such as a medical interview. Details about adverse events, such as the date of occurrence, degree of adverse events, causal relationship with the treatment, other treatments or medications that are suspected to cause the adverse event, and treatment of the adverse event, will be recorded in detail.

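### As printed, Table 1 puts the week-3 VAS (the primary endpoint) at the third injection and acupuncture session 7 of 9, whereas the text implies the end of treatment

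*Protocol article*

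**What the plan says.** The VAS section of the protocol article is brief: "Our primary end point is three-week VAS". Data collection adds: "Both the primary and secondary outcomes will be measured at baseline, and at one, three and five weeks thereafter".

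The Design section fixes the end of treatment indirectly: "The week five assessment will be performed two weeks after treatment cessation". The abstract says the same. The Interventions section plans one injection and three acupuncture sessions in each of three weeks. For the blood tests, the Safety section states: "All patients were evaluated two times, including the screening visit and after the termination of acupuncture".

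Table 1, under Data collection, is titled "Schedule of treatments and outcome measures throughout the trial". Weeks 1, 2 and 3 each have three columns. The acupuncture row has a tick in all nine. The injection row has a tick in the first column of each week. The week-3 ticks for VAS, PainVision, SF-MPQ, ODI and safety are also in the first week-3 column, and two more acupuncture ticks follow.

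**The concern.** The table and the text give different moments for the primary endpoint. A site working from the table visit by visit would record the week-3 VAS on the day of the third injection and seventh acupuncture session, with two sessions still to come. On the text, the score belongs after the whole course.

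The contrast of interest is acupuncture plus injection against injection alone. Unfinished acupuncture affects only the experimental arm. A score taken after that day's procedures may also be influenced by the mepivacaine in the injection, in both arms, and by needling just completed, in one arm.

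The safety sample in the same column would be drawn before the last two sessions. Safety is part of the stated primary aim, and sizing the full-scale trial is a main objective, so both results would be carried forward.

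**Working it through.** **1. Positions in Table 1.** The table has 12 time columns: 1 is baseline, 2–4 week 1, 5–7 week 2, 8–10 week 3, 11 week 4 and 12 week 5.

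| Row | Columns ticked |
|---|---|
| VAS, PainVision, SF-MPQ, ODI | 1, 2, 8, 12 |
| Safety | 1, 8 |
| Epidural injection | 2, 5, 8 |
| Acupuncture | 2 to 10 |

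**2. The plan's own totals.** From Interventions: 3 sessions × 3 weeks = 9, and 1 injection × 3 weeks = 3. The table has 9 and 3 ticks, so the totals agree. In the acupuncture row, each column is therefore one visit.

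**3. Treatment received at the week-3 VAS, column 8.**

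- Before that visit's treatment: sessions in columns 2–7, so 6/9 = 67%; injections in columns 2 and 5, so 2 of 3.
- After that visit's treatment: 7/9 = 78% of sessions and 3 of 3 injections.
- On the timing implied by the text: 9 of 9 and 3 of 3.

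The week-1 tick, in column 2, follows 0 sessions and 0 injections if taken before treatment, or 1 of each if taken after.

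**4. End of treatment from the text.** Week 5 is two weeks after cessation, and 5 − 2 = 3, so treatment ends at week 3.

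**5. Can the visit reading of the table fit the text?** Count days from baseline, so week 3 is day 21 and week 5 is day 35.

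- *The session-7 visit is day 21.* Sessions 8 and 9 come later, so treatment ends after day 21 and day 35 is less than 14 days after cessation. Illustration, assuming sessions on days 0, 2 and 4 of each week and a first session on day 7: session 7 is day 21, the last session is day 25, and 35 − 25 = 10 days.
- *Treatment starts on day 0.* On the same assumed pattern, session 7 is day 14, which is two weeks after baseline and not three. The last session is day 18 and 35 − 18 = 17 days.

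Read as visits, the table conflicts with the text in both cases.

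**6. Can the week-level reading fit?** Yes. With treatment from day 0, all nine sessions and all three injections are done by day 21. Day 35 is then 14 days after the end of the third treatment week, or 17 days after the last session on the assumed pattern. A safety sample at that point would also follow the end of acupuncture.

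**The case against.** The strongest reply is that the ticks mark weeks and not visits. Each week label spans three columns but appears in the first, and the assessment ticks follow the same pattern. A tick in a week-wide merged cell would look identical in the text available here, so counting columns cannot separate the two readings. The week-level reading also makes the safety row agree with the Safety section, and it fits a week-1 assessment made one week after baseline. This reading is plausible and cannot be excluded.

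It does not remove the point. The acupuncture row uses the same columns as single visits, and nothing tells the user of the table that the assessment rows follow another rule.

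It is also fair to say that visit windows and the order of procedures within a visit are details an article commonly leaves to the full protocol. Their absence is not the finding. The finding is a printed schedule that, read as it stands, disagrees with the text on the primary endpoint.

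A reader might go further and infer that same-day anaesthetic would dominate the scores or drive them towards zero. The documents give the content of the injection but no duration or size of its effect on pain. Both arms receive it, so by itself it favours neither. A reader might also take the 2 or 3 outstanding sessions of 9 (22% or 33%) as the share of the acupuncture effect lost. That needs equal benefit from every session, which the documents do not support.

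**Conclusion.** The point holds as a conflict between Table 1 as printed and the text, not as proof that the endpoint will be mistimed. On the visit reading, the primary VAS follows 6 of 9 sessions and 2 of 3 injections, or 7 of 9 and 3 of 3, and the safety sample precedes sessions 8 and 9. On the week-level reading there is no conflict, but the table does not show that this is meant. The counts rest on the column positions as printed. The day numbers rest on an assumed pattern of sessions and serve only as illustration.

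Severity is moderate. The trial is a 14-patient pilot, its planned analysis uses all four time points, and no significance level, power or sample-size figure changes. The correction still deserves making, because it concerns the primary endpoint and the estimate that the pilot is meant to supply.

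**What to change.** Reconcile Table 1 with the abstract and with the Design, Data collection, VAS and Safety sections:

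- Move the week-3 ticks (VAS, PainVision, SF-MPQ, ODI, safety) to a point after the ninth acupuncture session and the third injection. Set it at the same time from first treatment in both arms, since the control arm has no acupuncture sessions to count from, and not after a treatment given that day.
- Place the week-1 assessment one week after the start of treatment and before any treatment that day.
- Add one sentence stating this timing.

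The treatment schedule stays as it is. The cost is a table correction, one sentence, and at most one assessment moved by a few days.
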